## Abstract

Suicide prevention is an important public mental health issue that can be significantly brought forward by recent advances in psychological research methods and assessment. The project “TempRes” aims to harness the power of Ecological Momentary Assessment (EMA) to investigate the transdiagnostic risk and resilience factors associated with suicidal ideation drawn from the most recent research in suicide prevention and personality assessment. Participants will comprise the general population (planned: *N* = 100) and a risk group (patients currently in psychosomatic or psychiatric treatment) (planned: *N* = 50). After a comprehensive baseline assessment, they will complete up to ten short assessments per day over the course of 10 days at roughly equidistant intervals. In detail, the project examines the interplay of biography (previous suicidal behavior, experiences of childhood maltreatment), individual differences (level of personality functioning), and time-varying factors (entrapment, loneliness, mood) with respect to the emergence and fluctuation of suicidal ideation. There are two main research foci: First, the project will provide an operationalization and empirical verification of a core assumption of the *integrated motivational-volitional model of suicide* (IMV model). It will test whether the interaction of the time-varying predictors entrapment with loneliness (as a motivational moderator) explains reports of suicidal ideation over time. Second, it will be the first to examine *personality functioning* (a transdiagnostic, psychodynamically grounded conceptualization of vulnerability to psychological crises over the life span) as a time-invariant predictor of suicidal ideation assessed within an intensive longitudinal study design. The main analyses will be built on linear mixed models. The overarching aim of the project is to gain a better understanding of the psychological dynamics underlying suicidal ideation in different populations by bringing together concepts from different theoretical traditions. This will inform prevention efforts geared toward the general public as well as intervention in clinical populations.

## Introduction

Suicide is a global mental health issue that affects all strata of the population. It is estimated that over 700.000 people die by suicide every year (1). Despite decades of research and efforts to improve mental health care, persistent, or even rising numbers in some countries [e.g., (2, 3)] underline that suicidal ideation and behavior still pose great challenges. Furthermore, syntheses of empirical investigations of risk factors have not yet provided for the design of individual risk algorithms with satisfying accuracy (4). This is in part because of the relatively low case numbers of suicide outcomes in the general population, but also because of their complex, biopsychosocial etiology and challenges associated with their assessment. In the following, we describe how the most recent empirical evidence suggests that relevant progress in suicide research can be achieved through study designs that implement the following insights: first, multiple risk factors and/or protective factors work together, second, suicidal ideation and behavior are distinct entities, and third, suicidal ideation can fluctuate substantially. Going from there, we describe how the project TempRes (“Temporal variability of risk and resilience factors for suicidal ideation”) aims to make a contribution to the field by also integrating social-cognitive research traditions and psychodynamic concepts.

First, many epidemiologically-oriented studies have tested associations of suicide outcomes with other variables (4–6). However, a large proportion of risk indicators established this way are imprecise, for example, because they apply to large groups of the population [such as male gender). In addition, studies have reported distal risk factors (such as child maltreatment (7)] that might not directly exacerbate the risk of suicidal crises as their effects are altered by further mediating and moderating variables. Although necessarily reductionist study designs cannot possibly mirror the complexity underlying the emergence of suicidal crises in daily life, new insights could be gained by studying different risk factors in combination (8, 9). Respective statistical operationalizations could include stratified analyses (e.g., 10) which can give insight into group-specific risk constellations. Another option is the modeling of two (or more) variables' interplay using interaction terms [e.g., (10)]. Corresponding models could not just include relatively stable individual differences, but also time-varying environmental variables or mental and emotional states. This seems particularly appropriate against the background that psychological science has long conceived of distress or wellbeing, respectively, as the result of an interplay of the person and the situation: In Lewin's famous formula [B ~ (P;E)], behavior (B; extended to cognitions and emotions) is a function of the person (P) and their environment (E) (11). Previous research has highlighted important factors within each of these domains. A particularly comprehensive and differentiated synopsis is presented by the integrated motivational-volitional (IMV) model of suicide (12). The IMV model differentiates three phases [see Figure 1 in O'Connor and Kirtley (12) for a visual depiction]: The pre-motivational phase describes the broader context of biological, psychological, and social vulnerability and resilience factors shaping the risk of suicidal crises over the life span, analogous to classical diathesis-stress-models. It is followed by the motivational phase. The conceptualization of this second phase emphasizes that the emergence of suicidal ideation is a highly dynamic process involving the interplay of various factors, most of which are psychological in nature: If an individual experiences defeat or humiliation, their risk of suicidal ideation further hinges on their ability to cope with these feelings in an adaptive way (according to individual differences summarized under threat-to-self moderators). If they do not succeed in resolving this distressing subjective state, they could feel entrapped, meaning they see no way out. At this point, motivational moderators, such as social support, influence whether the individual can think of alternative ways to end their emotional pain (rather than ending their life). Lastly, the model includes a volitional phase in which self-destructive thoughts are acted upon (i.e., the person engages in suicidal behavior). Factors that govern the transition from the motivational to the volitional phase are called volitional moderators. As an example, they comprise access to means, i.e., suicide attempts will be facilitated if the person at risk has a firearm in their home.

**Figure 1 F1:**
[figure not shown]
Simplified depiction of the variables and associations that are the focus of the primary research goal. A reduced, specified version of the integrated motivational-volitional model of suicide [IMV model; O'Connor and Kirtley (12)] will be tested in the context of the project. The IMV model differentiates three phases: First, the pre-motivational phase describes the broader context of suicidal crises over the life span. Second, in the motivational phase, suicidal ideation is conceptualized as the result of the dynamic interplay of distressing emotional states and moderating factors that determine an individual's ability to cope with them. Lastly, the transition to suicidal behavior—the volitional phase—is shaped by further, specific risk factors (the volitional phase is not depicted here as the project focuses on suicidal ideation). All motivational phase variables will be assessed using Ecological Momentary Assessment.

Second, the distinction between suicidal ideation and behavior inherent in the IMV model must be emphasized. It is also a central part of two other current theories of suicidal ideation and behavior within the influential ideation-to-action framework (13), the Interpersonal Theory of Suicide (IPTS) (14) and the Three-Step Theory of Suicide (3ST) (15). This distinction reflects the state of the art of suicide research which has shown that risk factors for suicidal ideation and behavior are distinct (16, 17). Variables that govern the transition from the former to the latter are called volitional moderators within the IMV model and comprise e.g., access to means such as firearms (17). While suicidal behavior comprises non-lethal as well as lethal suicide attempts, suicidal ideation can manifest as passive (i.e., death wishes) or as active (i.e., the desire to engage in suicidal behavior). An instructive summary and guide of how different suicide outcomes should be denominated is provided by Silverman, Berman (18). To yield meaningful results that others can build on, it is important for research endeavors to clearly define and correctly assess the respective suicide outcome of interest instead of conflating different manifestations (e.g., by summarizing them under the umbrella term “suicidality,” which muddles the waters and hampers progress) (9).

Third, as noted above, previous research on suicidal ideation and behavior has provided a lot of information describing *who* is at risk (e.g., men, individuals who have experienced childhood abuse). By contrast, an important frontier concerns the question of *when* somebody is at risk (i.e., within-person variation). Within the context of suicide research, this is an especially meaningful question as suicidal crises have been shown to be transient states (19, 20). Hence, fluctuating suicidal ideation is not captured well by questionnaire assessments that instruct individuals to report mental distress over the course of the last weeks (either as an average or as days in a week on which they suffered from specific symptoms). In such cases, responses are also influenced by the emotional state in the here and now (21) and recall biases (22). For instance, reports of suicidal ideation which were made during the week did not always match responses in a questionnaire administered at the end of the week (using established instruments such as the Beck Scale for Suicide Ideation) (23). What is more, risk factors for suicidal ideation also vary over time, e.g., defeat and entrapment, central aspects of the motivational phase of the IMV model (24). Thus, a valid assessment of suicidal ideation and associated risk or protective factors needs to be change-sensitive. This applies to the questions which are asked (e.g., “How do you feel now?,” instead of “How did you generally feel over the course of the last month?”) and to the sampling method (e.g., multiple times a day instead of once every few weeks). Research designs that enable the study of psychological processes as they unfold in daily life are called ambulatory assessment (AA), Ecological Momentary Assessment (EMA), or daily life methods (25). Considerable technological advances in recent years have made them easier to administer, for example by using apps on participants' mobile phones. Consequently, there is now a large body of research using these methods in healthy and clinical populations, including individuals at risk for suicidal ideation and behavior (20, 26). The proportions of participants reporting suicidal ideation varied widely between different studies with intensive longitudinal designs, ranging between a fifth of participants and the entirety of participants (27). However, sample characteristics (such as whether participants were drawn from the community or a clinical sample) were more closely associated with studies' detection of suicidal ideation than the number of daily assessments or other design characteristics. Within the present study, we use the term EMA as it does not include any passive monitoring (e.g., of biomedical parameters), but the real-world and real-time aspects of the assessment are deemed the most important following Silvia and Cotter (25).

Lastly, there are seminal psychodynamic contributions to the understanding of both “normal” development and psychopathology, including suicidal crises [e.g., (28–30)]. In spite of attempts at building bridges between disciplines [e.g., (31, 32)], so far psychodynamic approaches have not been brought together with the major developments in the empirical study of suicidal ideation and behavior described above. However, recent advances in the operationalization of central psychodynamic concepts facilitate the integration of these perspectives. In particular, the project will investigate the role of the level of personality functioning. As a dimensional ascertainment of temporally stable, basic abilities or impairments, respectively, it has long been an important component of psychodynamic diagnosis and treatment planning. Since the reconceptualization of personality pathology in the upcoming eleventh revision of the International Classification of Diseases (ICD-11) and the DSM-5 Alternative Model for the Assessment of Personality Disorders (33), it has received increased attention. Besides informing about broad, health-related personality characteristics, the assessment of personality functioning could yield new insights into the between-and within-person factors underlying suicidal ideation. First empirical studies in patient samples (34, 35) that highlighted its transdiagnostic relevance for different suicide outcomes support this notion.

Building on previous research and following the considerations outlined above, the project TempRes uses an intensive longitudinal study design and focuses on suicidal ideation. Study assessments include the pre-motivational and the motivational phase of the IMV model: The more extensive assessment at study intake captures constructs that are assumed to be relevant time-invariant risk or protective factors, such as the level of personality functioning. In the following EMA module, assessments focus on psychological state variables (e.g., entrapment, loneliness) and the context (e.g., where participants are at the moment, whether someone is with them).

The primary research goal is the operationalization and empirical verification of a core assumption of the IMV model over time (Figure 1 depicts the main constructs of interest).

For this research goal, we will test the following hypotheses:

Hypothesis 1: According to premise 6 of the IMV model (detailed in 13), individuals who have intentionally self-harmed in the past report higher levels of the motivational phase variables (entrapment, loneliness, and suicidal ideation) than those who have not done so.Hypothesis 2: Motivational phase variables (entrapment, loneliness, and suicidal ideation) vary over time.Hypothesis 3: Entrapment is positively associated with suicidal ideation:Hypothesis 3.1 Feelings of entrapment are positively associated with suicidal ideation.Hypothesis 3.2 The relationship between entrapment and suicidal ideation is moderated by loneliness, i.e., it is particularly strong if people also feel lonely.

The secondary research goal concerns the exploration of the role of personality functioning. Since this part of the project cannot directly relate to previous studies with similar methodology, the hypotheses are less concrete: First, we will explore associations of personality functioning with established risk and protective factors from the pre-motivational phase (e.g., we expect impaired personality functioning to be associated with childhood abuse and neglect and with previous self-harm). Second, the level of personality functioning will be tested as a background factor, in the sense that greater impairments are assumed to be associated with higher levels of the motivational phase variables. However, it could also play a role as a moderator within the motivational phase: motivational moderators are defined as “factors that, when present and protective, allow the trapped individual to see alternatives, a more positive future and less pain” (12). Respective constructs included implicit and explicit attitudes as well as negative self-appraisals, both of which conceptually overlap with measures of personality functioning such as the OPD-Structure Questionnaire (OPD-SQS) (36). In addition, studies have suggested an intermediate role of personality functioning, for instance, it linked childhood abuse and neglect with mental distress later in life in a cross-sectional population study (37) and with inhibition difficulties in an experimental go/no-go task (38) in patients with depressive and personality disorders and healthy control participants.

## Methods and Analysis

This is a prospective, observational study with an intensive longitudinal design. Participants are recruited from the general population and patients treated at the University Medical Center Mainz (Department of Psychosomatic Medicine and Psychotherapy, Department of Psychiatry and Psychotherapy).

### Selection of Participants

With the combination of a population sample and a patient sample, we aim to achieve variation regarding the variables of interest: On the one hand, rates of suicidal ideation (assessed using EMA) and behavior (assessed retrospectively) in the general population are relatively low (e.g., 9). In a recent survey of a representative German community sample, we found rates below 10% (using the PHQ-9 item) (39) whereas an analysis of the same item based on unpublished routine data of 724 patients treated at the Department of Psychosomatic Medicine and Psychotherapy of the University Medical Center Mainz over the course of 4 years showed rates of 41%. They are considerably higher in clinical populations. On the other hand, individuals in psychiatric and psychosomatic-psychotherapeutic (inpatient) treatment show comparatively greater impairments in personality functioning (40). As we intend to study associations of personality functioning with suicidal ideation and established risk and protective factors (including more complex associations proposed by previous research, such as moderating or mediating effects), it will be beneficial to recruit a substantial number of mentally healthy individuals with higher levels of personality functioning as well.

Inclusion or exclusion criteria, respectively, are the same for the general population and the patient sample. Given that the study focuses on transdiagnostic risk and resilience factors, participation will be open to a broad range of individuals. However, participants need to be able to understand and complete the assessments as intended. This is why individuals with current substance use disorders and psychotic symptoms are not considered eligible. Further exclusion criteria are insufficient knowledge of the German language and the absence of a smartphone for personal use. Lastly, the study focuses on the motivational phase in which suicidal ideation arises. It does not include the study of (risk and protective factors associated with) suicidal behavior/self-harm. As the technical realization of the study neither allows for the personal identification of single participants by the research team nor for the processing of data in a way that would allow for real-time-monitoring and intervention. Therefore, we decided that for safety reasons, acutely suicidal individuals cannot take part.

### Recruitment and Consent Procedure

The recruitment of participants of the *population sample* will predominantly use online channels. A short description of the study and contact information will be posted online (e.g., on the website of the Department of Psychosomatic Medicine and Psychotherapy of the University Medical Center Mainz and the Study Center for Clinical Trials in Mental Disorders of the University Medical Center Mainz) and circulated via social media. In order to recruit *patients*, the same information will be included in a leaflet that will be distributed in waiting areas and/or handed directly to patients (in treatment at the Department of Psychosomatic Medicine and Psychotherapy or the Department of Psychiatry and Psychotherapy of the University Medical Center Mainz) by clinical and research staff. Additionally, posters will be distributed on the clinic premises. We will actively seek to oversample male patients to achieve a gender-balanced sample, as patients treated in mental health care, e.g., at the Department of Psychosomatic Medicine and Psychotherapy are predominantly female.

After a short eligibility check, individuals will be informed about the study in detail (patient sample: in person by the Principal Investigator (PI) or a research assistant; population sample: online in writing or, if desired, also by phone). All eligible individuals will be informed that data will be gathered and analyzed anonymously and that they can withdraw from the study at any time without explanation without any negative consequences. They will have the opportunity to ask questions. Only then will they be asked to fill out an informed consent form (patient sample: on paper, a copy will remain with them; population sample: online).

### Ethics and Safety Aspects

The study was designed in line with expert recommendations for intensive longitudinal studies (including in at-risk populations) (41, 42). It follows guidelines for good clinical practice and fulfills the ethical principles of the declaration of Helsinki. Data is collected in a parsimonious, anonymous way combining the Samply Research app (43) with the SoSci Survey platform (44). Participants are never asked to enter identifying information such as their names. All procedures are in line with the General Data Protection Regulation (GDPR). Participant information and consent forms were created in line with the recommendations of the German Psychological Society (DGPs). The study contents and procedure were approved by the ethics committee of the Department of Psychology of the Johannes Gutenberg-University Mainz (number 2021-JGU-psychEK-019).

Before participants are enrolled, a feasibility study will be conducted (*N* = 5–10) to test the technical implementation of data collection and management. Only afterward will participant recruitment start, first for the population sample.

The study has been registered in the research registry of the University Medical Center Mainz (Forschungsregister FoR.UM) which is managed by the interdisciplinary center for clinical trials (Interdisziplinäres Zentrum Klinische Studien, IZKS) (number 21-00292). Registration includes information about the status of the project and the responsible PI and research staff. It allows the site management organization to track the numbers of screened, included, and excluded participants.

The study is observational and does not include any interventions. However, it deals with distressing psychological states. This is why the first page of the online questionnaire administered in the population sample contains information about emergency contacts (e.g., the German telephone counseling service Telefonseelsorge). Patients will be in the clinic setting for the duration of the study, where a safety protocol is in place (standard operating procedures for keeping acutely suicidal patients safe, developed by trained staff that includes clinicians and researchers with decades-long experience in working with individuals with severe mental disorders).

Along these lines, we find it important to rebut persistent “suicide myths” that asking about suicidal ideation would amplify a suicidal crisis (i.e., that it is iatrogenic). This is not the case: Previous research has found that confrontation with respective stimuli did not contribute to higher levels of suicidal ideation. Disclosure of suicidal ideation was instead associated with relief (45). Repeated assessment of suicidal ideation in the context of AA studies did not increase suicidal ideation either (46). However, it has been noted that digital monitoring studies of mental health outcomes pose particular ethical issues, such as whether researchers should intervene, and if so, how, if participants report suicidal ideation or self-harm (impulses) (42, 47). There are no established best practices yet, but according to a recent review, sixty percent of previous studies used automated pop-up notifications while forty percent of studies did not monitor participants' responses (47). While experts have recommended daily monitoring in at-risk populations (41), the technical implementation of data collection and lack of resources to screen and adequately react to incoming data in the present study did not allow for real-time monitoring either. Therefore, we decided to exclude acutely suicidal individuals from participation due to safety concerns.

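### Emergency contacts are described only for the population sample, while patients rely on a clinic stay that no stated criterion secures. Show the contacts to both samples, including in the EMA survey.

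*Protocol article*

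**What the plan says.** Ethics and Safety Aspects notes that the study concerns distressing states and describes a different safeguard for each sample. For the general population, "the first page of the online questionnaire administered in the population sample contains information about emergency contacts". For patients, "Patients will be in the clinic setting for the duration of the study, where a safety protocol is in place".

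Three other statements bear on the second safeguard:

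- **Who the patients are.** The Abstract defines the risk group as "patients currently in psychosomatic or psychiatric treatment". Recruitment and Consent Procedure describes them as "in treatment at the Department of Psychosomatic Medicine and Psychotherapy or the Department of Psychiatry and Psychotherapy", reached by posters and by leaflets that staff hand out or leave in waiting areas.
- **What they must satisfy.** Selection of Participants says "Inclusion or exclusion criteria, respectively, are the same for the general population and the patient sample". The exclusions listed are current substance use disorder, psychotic symptoms, insufficient German, no personal smartphone and acute suicidality.
- **What the team can see.** The same section says that "the technical realization of the study neither allows for the personal identification of single participants by the research team". Both it and Ethics and Safety Aspects state that responses are not followed in real time.

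**The concern.** The article's reason for giving contacts, that the study deals with distressing states, applies at least as much to patients as to the general population. Yet the contact page is described only for the sample with the lower expected rate of suicidal ideation. The patients' safeguard works through place: it covers them while they are in the clinic. Nothing in the stated criteria requires inpatient status or a remaining stay long enough to cover the study, and the article does not say what happens on leave or early discharge.

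The EMA prompts ask about wishing to die and wishing to kill oneself. They arrive on the participant's own phone between 8 a.m. and 10 p.m., wherever that person is. Since nobody reads the answers as they come in, help depends on the participant seeking it or on staff learning of the distress in some other way. A patient away from the clinic at that moment would have neither of the two measures the article describes. At stake is a simple safeguard for individual participants, not the validity of any analysis.

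**Working it through.** This is mainly a comparison of text. The plan gives no figure for patients outside the clinic, so there is none to reproduce.

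**1. Does any stated criterion secure the clinic stay?** The five listed exclusions apply to both samples, and none concerns setting or length of stay. The Abstract and the recruitment section ask only for current treatment. Selection of Participants mentions inpatient treatment once, in parentheses, when citing differences in personality functioning; that is not a criterion. The stay therefore rests on the one sentence in Ethics and Safety Aspects.

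**2. How long must it last?** Study Assessments places the baseline before the first EMA day, then 10 EMA days, then an end assessment after the last: 1 + 10 + 1 = about 12 calendar days.

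**3. Can an EMA answer trigger the clinic's procedures?** No. Participants cannot be identified and data are not watched live. This holds for a patient on the ward too.

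**4. Would copying the first page be enough?** Only partly. The article does not say which module the page belongs to. The intake questionnaire is the natural reading, because EMA Module describes a single survey link, the same in every push message, with no distinction between samples. On that reading the page is seen once, before EMA begins, and is not on screen when a prompt arrives. Contacts available at the prompt have to sit in the EMA survey itself.

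**5. Which sample carries the higher risk?** Inputs are from Selection of Participants and Power and Sample Size Considerations:

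- Patients: routine data on 724 patients of one department "over the course of 4 years showed rates of 41" per cent on the PHQ-9 item.
- Community: "we found rates below 10% (using the PHQ-9 item").
- Planned numbers: 50 patients and 100 from the general population.

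| Quantity | Calculation | Result |
|---|---|---|
| Patients endorsing the item | 0.41 × 50 | 20.5 |
| Count behind the 41% | 0.41 × 724 = 296.8 | about 297 |
| Wilson 95% interval for 297/724 | – | 37.5% to 44.6% |
| That interval applied to 50 patients | 0.375 × 50; 0.446 × 50 | 18.7 to 22.3 |
| Binomial SD among 50 patients | √(50 × 0.41 × 0.59) | about 3.5 |
| Approximate range for a single sample of 50 | 20.5 ± 1.96 × 3.5 | about 14 to 27 |
| Population participants endorsing it | below 0.10 × 100 | fewer than 10 |
| Ratio of rates | 0.41 / 0.10 | more than 4 |

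The 41% comes from one of the two departments and from routine patients before the acute-suicidality exclusion, so the enrolled rate may be lower. The community rate is from a representative survey, whereas the study's population sample is self-selected and may differ. The table supports the ordering of risk and nothing more. It counts people with ideation, not people outside the clinic.

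**The case against.** The sentence on the clinic setting can fairly be read as a design commitment, with patients deliberately given a different and arguably stronger safeguard than online participants. The shared list of criteria could not contain a clinic-stay requirement without excluding the whole population sample, so its absence there says little about how the patient arm is run. Patients are informed in person and keep a copy of their consent form. That form, the patient information and the clinic's procedures are not shown, and an article would not normally reproduce them. Ethics approval was obtained.

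Most of this stands, and it sets the limit of the point. A reader might infer that outpatients are enrolled, that patients are discharged during EMA, or that patients have no emergency information. The documents support none of these: no patient outside the clinic is shown, and contacts may be given by another route. Nor do the treatment-based definitions contradict the clinic sentence, since patients in treatment may all be inpatients.

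What remains does not rest on silence. The article states which sample gets the contact page, and for the other sample it names a substitute that works only while the patient is in the clinic. Showing contacts to both samples helps whether or not the commitment holds for every patient, and at worst repeats what the consent papers already say.

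**Conclusion.** The point holds as a low-severity safety improvement. As described, emergency contacts go to the population sample only, and the patients' cover depends on a stay of about 12 days that no stated eligibility or recruitment criterion secures. Patients do have the clinic's procedures while they are there, and acutely suicidal people are excluded at entry, so no failure is shown.

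The number of patients who might be away from the clinic is unknown. For scale only, each 2 percentage points of the planned 50 is one person (0.02 × 50 = 1). It would be tempting to read the 20 or so expected patients with ideation as 20 patients without protection. That does not follow: the figure shows that patients are the higher-risk sample and says nothing about where they will be.

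The conclusion assumes that the contact page belongs to the intake questionnaire and that the article's account of it is complete for the survey itself.

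**What to change.** 1. Show the existing emergency-contact information to both samples at intake. Baseline Assessment describes one set of content that records how each participant was recruited, so the page can appear regardless of sample.
2. Add a short contact line to the EMA survey that every push message opens, or to its closing page, so that it is available at each prompt wherever the participant is. Without this step, the contacts would be seen only once, before EMA starts.
3. Optionally, the study's clinicians could state the expected length of stay at enrolment and what applies on leave or early discharge.

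The cost is close to zero: reuse of an existing page, one added line in the survey, and notification of the ethics committee if it requires this. No item, assessment time, sample size or analysis changes.
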